### Recruitment and Sample Size Justification

Objectives 1, 2, and 3 will use convenience sampling to recruit participants through different channels, including clinics, patient foundations, community-based organizations, and professional associations [39]. For example, patient participants will be introduced to the study by their health care service provider (eg, physician, nurse, or social and community worker) during their visits. Informational materials such as study flyers and a video (Multimedia Appendix 4) showcasing the MARVIN chatbot will be disseminated via email, newsletters, or a website.

Participants will be required to consent before engaging in each objective. For objectives 1 (development) and 2 (usability), interested individuals can reach out to the study coordinator. Detailed study procedures, eligibility checks, and consent collection will be facilitated by the study coordinator for those expressing interest. Verbal consent may be adopted for participants who continue from objective 1 to objective 2. This will be obtained remotely through teleconference with an impartial witness to ensure compliance with all aspects of free and informed consent. Following the co-construction approach [30], a co-construction design committee consisting of researchers, health care professionals, and volunteer patient partners will be formed starting from objective 1 to carry out the subsequent development. The sample size for objective 1 is 20 participants to ensure saturation for the needs assessment focus groups [40], whereas 30 participants will be recruited to complete the corresponding usability test for objective 2. This sample size is common for pilot studies and satisfies the minimum size recommended in the literature [41,42].

For objective 3 (implementation), an optimized version of the chatbot will be accessible from the web around the clock, 7 days a week, for translational research. As currently the MARVIN chatbots will be only released in Canada, recruitment will be exclusive to the Canadian population, and participants will engage in an electronic consent process through the MARVIN chatbots. Before using the chatbot, individuals will be required to review and accept MARVIN’s privacy policy (Multimedia Appendix 5). Subsequently, they will be asked to review an electronic version of the information and consent form and then answer the following verification questions for eligibility criteria 1 to 3 via the chatbot: (1) *Are you at least 18 years old?* (2) *Are you comfortable using English or French while communicating with the chatbot?* (3) *Do you agree to participate in the study as described above?* The remaining criteria (4 to 8) will be met once users connect to the chatbot. Should participants agree to participate, their responses will be securely recorded in a separate encrypted database on the MARVIN cloud servers and synchronized to the electronic enrollment log. If users opt not to participate, no records will be kept. As a Facebook account will be a prerequisite for using the chatbot, no further measures will be taken to detect or prevent the possibility of multiple identities. The target sample size of 30 to 150 participants was obtained based on the usability, acceptability, and appropriateness outcomes, which are considered key outcomes for this objective. The analysis involves a 1-sided Student *t* test (1-tailed) evaluating whether the corresponding average attains a predetermined threshold. A power analysis for a 1-sample *t* test is then performed, with 80% power and a 5% significance level. Within the targeted sample size (30≤n≤150), small to moderate standardized effect sizes (0.2≤Cohen *d*≤0.5) are detectable in the total sample with the aforementioned statistical power.

Regarding objective 4 (partnership evaluation), upon completion of each objective, an email invitation will be sent to organize focus groups with stakeholders involved in the chatbot co-construction design committee.

The information and consent forms outline detailed study procedures, anticipated benefits, and potential risks. All template versions are available in Multimedia Appendix 6. Participants may withdraw from the study at any time after providing informed consent. This information will be recorded in the electronic enrollment log, and the related privacy management and protection measures will be detailed later. To protect the participants’ personal data and identity, no identifying information will appear in any manuscript or report from this study.

### Intervention: Status Quo of the MARVIN Chatbot

#### Overview

Running on Messenger 24/7 for free [43], MARVIN was created as a bilingual chatbot in both English and French trained to converse with people with HIV on the following self-management aspects: (1) guidance for antiretroviral therapy medication (with regard to time management, dosing, drug interactions, and medication reminders, among other things), (2) antiretroviral therapy management when traveling, and (3) common HIV-related knowledge (eg, symptoms, modes of transmission and prevention, and vaccination recommendations).

The team conducted the first pilot project (MUHC REB 2021-7191) in April 2021 with 28 people with HIV receiving treatment at the MUHC. The study results showed that MARVIN was tailored to patient requirements and was easy to use and approachable but that the chatbot’s comprehension had limits [32]. For example, if a patient asked a question that was outside the range of topics in the question bank or was worded differently, the chatbot did not always understand it. Nonetheless, considering the development phase, participants reported being satisfied with MARVIN and mentioned that they intended to use it. Thus, by talking to the on-call chatbot, people with HIV could obtain the information they needed for self-management.

#### AI Algorithms and Strategies

MARVIN is currently being developed using the Rasa platform (Rasa Technologies Inc), an open-source machine learning framework for automating text- and voice-based virtual assistants [44]. As shown in Figure 3, MARVIN’s architecture comprises 3 distinct modules: natural language understanding, dialogue management, and response selection. Together with a self-built knowledge database, these modules are used to process the message input and generate the message output.

The acceptable input data include natural language in text form as well as some auxiliary expressions commonly used for chatting (eg, emojis such as the thumbs up, smiley face, and sad face). The initial natural language understanding module allows MARVIN to semantically process the input messages through different algorithms such as text preprocessing, entity extraction, and intent classification. The current training data set encompasses a corpus of >3000 questions covering >30 topics. Figure 4 shows an example of text processing. The entity extraction mechanism enables the chatbot to obtain structured information (eg, date, time, and medication name) from the input messages, whereas intent classification helps MARVIN discern the purpose of the information received.

In particular, MARVIN adopts the *FallbackClassifier* algorithm as a fail-safe measure for unprocessable input forms such as images, videos, and sounds. It is also activated when the confidence level of the anticipated intent falls below an established threshold. If the input remains incomprehensible after 2 attempts, the chatbot responds in a uniform manner: “I’m sorry, I can’t understand your question right now. Please contact a healthcare professional if you need to.” As illustrated in Figure 5, this approach reduces the probability of the chatbot taking incorrect actions when confronted with ambiguity.

The machine learning–driven conversation management determines MARVIN’s subsequent actions based on the input message and context in the conversation. A hybrid strategy of the *memoization policy* and *rule policy* was adopted [45]. The *memoization policy* remembers the decision trees from the training data and predicts the next action in conjunction with the derived intention: asking clarifying questions, providing tailored answers, and taking a fallback action. MARVIN can also remember and analyze a certain number of rounds of dialogue to support the prediction. Meanwhile, the *rule policy* handles pieces of conversation that should always follow the fixed behavior defined in the training data (eg, question: *What is ART?* answer: *It means AntiRetroviral Therapies*).

The final response selection module enables MARVIN to select messages predefined by the health care team as output messages. All the data required for processing by the first 3 modules are stored in the knowledge database—after each decision is made in the processing module, MARVIN communicates with the database to compare, extract, or save the data. All data are selected, edited, and validated by the medical team and then processed and added to the database by the development team. Data types include the previously mentioned antiretroviral therapy management–related information, decision trees for different problem scenarios, and predefined answers. An example of response selection from predefined answers in MARVIN is shown in Figure 6.

**Figure 3 figure3:**
[figure not shown]
Operation process of MARVIN.

**Figure 4 figure4:**
[figure not shown]
Example of text processing in MARVIN.

**Figure 5 figure5:**
[figure not shown]
Examples of MARVIN handling bad inputs: (A) fallback policy; (B) redirection after 2 failed attempts.

**Figure 6 figure6:**
[figure not shown]
Conversation example with MARVIN.

#### Content Development and Improvement Process

To train MARVIN to understand different types of questions and provide relevant and accurate answers, we assembled a multidisciplinary team of 2 clinicians (ML and [name]), 2 pharmacists ([name] and RT), 4 patients, 2 engineers (YM and SA), and multiple developers. Each group’s expertise played a crucial role in chatbot content development and continuous improvement: (1) health care professionals validated the medical accuracy of the answers and information given by the chatbot; (2) together with patient partners, they collaborated to identify common self-care challenges; (3) engineers then assisted in building decision models and preparing chatbot training data based on identified problems; and (4) finally, engineers and patients collaborated on testing and refining the chatbot based on feedback, completing the interdisciplinary cycle. This multidisciplinary team allowed us to ensure the accuracy and quality of the information provided as well as conduct holistic research and ongoing evaluation of the chatbot to promote its long-term usability.

#### The Interface

Messenger has 1.3 billion monthly active users worldwide exchanging 8 billion messages per day [46]. This indicates a robust familiarity with the Messenger interface among the population, simplifying their grasp of the platform’s specifications and interaction capabilities, ultimately favoring the uptake of the MARVIN chatbots. In addition, the versatility of Messenger, compatible across smartphones, tablets, and desktops, reduces the potential risk of participant exclusion because of hardware limitations. Nevertheless, the privacy concerns brought up with Facebook in the past may make people hesitant, which could be one of the potential barriers to the implementation of Messenger for health purposes. Indeed, other user interface options such as a stand-alone mobile app, a web page, or other third-party applications (eg, Telegram or Instagram) are under consideration. As the study proceeds and evolves, relevant changes will be implemented as necessary.

### Main Study Process

#### Overview

Multimedia Appendix 7 illustrates the entire study process.

#### Objective 1: Co-Construction of the MARVIN Chatbots

##### Overview

Objective 1 is intended to obtain a stabilized version adapted to the health care context for the subsequent objectives. Similar to the original MARVIN’s development, it will follow 3 steps: user needs assessment, knowledge database creation, and continuous improvement of the prototype.

The expected duration of participant involvement in objective 1 is 4 months.

##### Step 1: Needs Assessment

Four 2-hour focus groups will be organized with 5 participants each led by a trained interviewer. Participants will first be shown a demonstration of the current MARVIN describing the interface, dialogue process, and other instructions for use. Semistructured focus groups will then be conducted to identify use scenarios, topics related to integration, and user expectations and preferences for chatbots.

The co-construction design committee will then be formed and meet every 2 weeks to participate in design tasks. The team may also contact them via email with specific questions.

##### Step 2: Knowledge Database Creation

A knowledge database will be built based on the results of the needs assessment, which is the core of each new chatbot. This database will include a bank of different questions, plausible answers, and necessary conversation templates. Among the most important components of this knowledge database is a corpus of qualified and trusted answers. The challenge is to generate medically accurate information that is easy to understand and sufficiently colloquial while maintaining professionalism. These data will be collected from different sources and validated by the co-construction design committee for adoption to ensure that the chatbot can respond with appropriate output [29,30]. A total of three 2-hour co-construction workshops will be conducted.

##### Step 3: Testing, Validation, and Continuous Improvement

The team of engineers will work closely with the co-construction design committee through development workshops to test the prototype’s performance, especially its quality and safety. Participants will be invited to converse with the test prototype and complete an assessment. Such an approach will facilitate the continuous improvement of the prototype and the addition of new features (eg, user interface, questioning methods, and confidentiality measures) as necessary. Thus, each chatbot will evolve in real time during this step. A total of three 2-hour development workshops will be conducted.

It is important to note that, given the nature of software development engineering, steps 2 and 3 will be a continuous cyclic process. The research team will need to continually update the MARVIN chatbots based on feedback from the co-construction design committee on new requirements, improvement ideas, and technology updates.

##### Quantitative Data Collection and Analysis

During each development workshop, co-construction design committee members will perform a quick descriptive assessment of the tested prototype using the adapted Mobile App Rating Scale for health-related apps [47] (Multimedia Appendix 8).

The scale has 28 items (range 1-5) in 6 sections covering subjects including engagement, functionality, esthetics, information, subjective quality, and health-related quality. Item scores will be averaged to obtain a score for each section and an overall score. It has shown an excellent internal consistency (Cronbach α=.938) and interrater reliability (2-way mixed intraclass correlation coefficient=0.920, 95% CI 0.797-0.987) for the independent overall score ratings of 37 different digital health tools [47]. On the basis of developer recommendations, we will consider a successful prototype for testing to have an average score of at least 4 for the sections on information and health-related quality, as well as an overall average score of 4, as they are identified as key indicators of prototype safety.

##### Qualitative Data Collection and Analysis

Throughout the study, participants will have the option to take part in either English or French focus groups and workshops. All activities will be moderated by an experienced researcher with an assistant, digitally audio recorded, and manually transcribed verbatim for analysis while removing any nominal information provided to protect the participants’ identity. NVivo R1 (QSR International) will be used for qualitative data management.

Participants will also receive transcripts of the sessions in which they participated to ensure the trustworthiness of these data. Therefore, they will have the opportunity to challenge information that is perceived as incorrect. This will also allow them to verify that no information that could potentially identify them was inadvertently retained [48].

A focus group guide will be developed for each substudy considering its specific setting. Focus groups will be analyzed using an inductive thematic analysis approach to gather user recommendations (ie, topics to be addressed, expected conversational style, and desired features). Qualitative workshop data will contribute to thematic analysis in pursuit of objective 4.

#### Objective 2: Usability Assessment

##### Overview

Although a usability study among people with HIV has already been conducted [32], usability will be evaluated for other individual chatbot substudies following the same methodology. During this stage, no updates will be made to the chatbots unless (1) the chatbots are not available because of force majeure (eg, host server failure or algorithm dependency update), in which case the team will implement updates to ensure the proper conduct of the study; (2) the results indicate suboptimal usability, in which case we will update the version and repeat the usability study; or (3) new medical information emerges that could benefit participants or prevent harm. Any such event will be documented in detail.

The expected duration of participation for objective 2 is 1 month. At enrollment, 30 participants will be required to complete an initial sociodemographic questionnaire. They will be given a training session and a user guide with instructions on how to access MARVIN via Messenger and the topics of questions they can ask MARVIN. Participants will be enrolled for a 3-week period of interacting with MARVIN by having at least 20 conversations, the topics of which will be specified in each subprotocol. Quantitative data will be collected using a usability survey once their 20 conversations are recorded.

Participants will be free to complete the tasks at any time during this 3-week period. If the chatbot does not receive a message from them within a week of their most recent conversation, it will proactively send a reminder. There will be no active third-party human involvement in the entire testing process between the chatbot and participant user except in the case of user-initiated requests (eg, to solve unexpected bugs).

In week 4, a total of 3 focus groups with 5 randomly selected participants each will be conducted to explore MARVIN’s usability in greater depth and in the participants’ own words. In total, 3 focus groups can capture at least 80% of the themes, which is sufficient saturation for a usability study [49].

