**Methods:**

The MARVIN chatbots study has an adaptive platform trial design consisting of multiple parallel individual chatbot substudies with four common objectives: (1) co-construct a tailored AI chatbot for a specific health care setting, (2) assess its usability with a small sample of participants, (3) measure implementation outcomes (usability, acceptability, appropriateness, adoption, and fidelity) within a large sample, and (4) evaluate the impact of patient and stakeholder partnerships on chatbot development. For objective 1, a needs assessment will be conducted within the setting, involving four 2-hour focus groups with 5 participants each. Then, a co-construction design committee will be formed with patient partners, health care professionals, and researchers who will participate in 6 workshops for chatbot development, testing, and improvement. For objective 2, a total of 30 participants will interact with the prototype for 3 weeks and assess its usability through a survey and 3 focus groups. Positive usability outcomes will lead to the initiation of objective 3, whereby the public will be able to access the chatbot for a 12-month real-world implementation study using web-based questionnaires to measure usability, acceptability, and appropriateness for 150 participants and meta-use data to inform adoption and fidelity. After each objective, for objective 4, focus groups will be conducted with the design committee to better understand their perspectives on the engagement process.

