##### Quantitative Data Collection and Analysis

The initial questionnaire for objective 2 will gather fundamental sociodemographic information (eg, year of birth, preferred language, gender, and ethnic group identity) and digital technology use (Multimedia Appendix 8).

Descriptive statistics will be used to depict the sociodemographic characteristics and digital technology use of the participants. Continuous variables will be reported using measures such as minimum, maximum, mean, and SD. In the case of ordinal and nominal qualitative variables, we will report both counts and proportions.

Global usability will be collected using 2 validated scales: the *shorter version of the Usability Metric for User Experience* (*UMUX-Lite*) [50] and the *Acceptability E-scale* (*AES*) [51] (Multimedia Appendix 8).

Usability is defined in part as “the extent to which a product can be used to be effective, efficient, and provide users’ satisfaction within its defined goal” [52]. The UMUX-Lite is a 2-item questionnaire answered on a 7-point Likert scale that is deemed appropriate for use in the evaluation of health technology [53]. The items ask whether the chatbot meets user needs and about perceived ease of use.

Acceptability is related to how agreeable, palatable, or satisfactory an intervention is perceived to be by stakeholders and is also considered part of global usability [14]. The AES contains 6 items rated on different 5-point Likert scales. It is a validated measure of the acceptability and usability of computer-based interventions for health care populations. Items evaluate, for example, how easy and enjoyable the innovation is to use, how helpful it is, and whether the amount of time to engage with it is acceptable.

As continuous outcomes, both usability and acceptability will be summarized using the minimum, maximum, mean, and SD. The sample mean of each global usability outcome will be compared with its recommended usability thresholds—68/100 for the UMUX-Lite score and 24/30 for the AES score—using a Student *t* test. It will test the null hypothesis that the average UMUX-Lite score is ≤68 and that the average AES score is ≤24. A significance level of 5% will be adopted.

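### The Objective 2 usability survey is tied to the 20th conversation and has no other stated time point, so early stoppers give no score and the usability means are probably too high

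*Protocol article*

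**What the plan says.** All references are to the Protocol article.

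- **Exposure** (Objective 2, Overview): "Participants will be enrolled for a 3-week period of interacting with MARVIN by having at least 20 conversations".
- **Survey trigger** (same section): "Quantitative data will be collected using a usability survey once their 20 conversations are recorded". No survey is described at the end of week 3 or at withdrawal.
- **Inactive users** (same section): "If the chatbot does not receive a message from them within a week of their most recent conversation, it will proactively send a reminder". Otherwise people step in only when the user asks.
- **Sample size** (Recruitment and Sample Size Justification): "30 participants will be recruited to complete the corresponding usability test for objective 2". The reason given is that "This sample size is common for pilot studies and satisfies the minimum size recommended in the literature". No allowance for non-completion is stated.
- **Analysis** (Objective 2, Quantitative Data Collection and Analysis): "The sample mean of each global usability outcome will be compared with its recommended usability thresholds", namely "68/100 for the UMUX-Lite score and 24/30 for the AES score". The nulls are one-sided (mean at or below the threshold), tested by t test at 5%.
- **Use of the result**: the Abstract says "Positive usability outcomes will lead to the initiation of objective 3". Study Design bases the decision to carry the same version forward on the Objective 2 results. The Objective 2 Overview says that suboptimal usability leads to an update and a repeat of the usability study.

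**The concern.** The survey carries both global usability scales and the Technology Acceptance Model scales. If it is released by the 20th conversation, having a score depends on having persisted, and persistence is itself partly a result of usability. UMUX-Lite asks whether the chatbot meets needs and is easy to use. AES asks, among other things, whether it is enjoyable and whether the time it takes is acceptable. A user who would answer no to these has reason to stop early. The article's account of the pilot (Intervention: Status Quo of the MARVIN Chatbot, Overview) names such a reason: the chatbot did not always understand questions that were off topic or worded differently.

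The means compared with 68 and 24 would then describe people who carried on, and would probably lie above the mean for everyone who tried the chatbot. A version with marginal usability would be more likely to look good enough for Objective 3. Because this is a master protocol, every substudy that runs Objective 2 by the same method inherits the rule.

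**Working it through.** **1. The plan's own figure.** The article gives no power figure for Objective 2. The only one is for Objective 3: standardized effects of 0.2 to 0.5 detectable for n from 30 to 150, one-sample t test, one-sided 5%, 80% power. With the noncentral t distribution, power = 1 − F(t(0.95, n−1); n−1, d√n). The smallest d at 80% power is 0.465 for n = 30 and 0.204 for n = 150, so the stated range reproduces. It is not at issue. The question here is who is scored.

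**2. Inputs.** From the article: n = 30, thresholds 68 and 24, one-sided 5% t test, scores only after 20 conversations. Not in the article, so assumed:
- completion proportion c of 0.9, 0.8 or 0.7;
- correlation r between a participant's score and the propensity to complete, 0.3 to 0.7;
- inter-scale correlation 0.7, where both scales are considered;
- SD 18, used only to express the shift in UMUX-Lite points. The rates below do not depend on it, because the true mean is set at the threshold.

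**3. Shift in the completer mean.** With score and propensity bivariate normal, and completion meaning propensity above the (1−c) quantile, the completer mean exceeds the all-enrolled mean by r × φ(z)/c SD, where z is the c quantile of the standard normal.

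- c = 0.9: φ(z)/c = 0.1755/0.9 = 0.195. At r = 0.5 the shift is 0.097 SD, or 1.8 points (0.097 × 18).
- c = 0.8: φ(z)/c = 0.2800/0.8 = 0.350. At r = 0.5 the shift is 0.175 SD, or 3.15 points, giving a completer mean of about 71.2 against a true 68.

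**4. False-pass rate** by simulation of 30 enrolled, true mean(s) exactly at the threshold, t test on completers. Ranges run over r = 0.3 to 0.7.

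| Completion | One scale | Both scales must pass |
|---|---|---|
| 100% | 5% | about 2% |
| 90% | 9-18% | 4-9% |
| 80% | 13-36% (22% at r = 0.5) | 6-23% |
| 70% | 17-55% | 9-40% |

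At 95% completion the single-scale rate is about 7-11%.

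**5. Below the threshold.** With a true mean of 65, SD 18, 80% completion and r = 0.5, the single-scale pass rate rises from 0.5% to about 5%.

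**6. Cross-check with a simpler model.** Let a share q not complete and score D within-group SDs below completers, with the all-enrolled mean at the threshold. Completers then sit qD above it, and the test has m = 30(1−q) participants. For q = 0.2 and D = 1: m = 24, shift 0.2, noncentrality 0.2 × √24 = 0.98, pass probability 24%. Over D = 0.5 to 1.5 the single-scale rate is 8-19% at q = 0.1, 12-41% at q = 0.2 and 16-64% at q = 0.3. Direction and order of size agree with step 4.

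**The case against.** **The trigger is a timing statement, not an exclusion rule.** The article does not say that only those who reach 20 conversations are surveyed, and it defines no analysis set. Subprotocols are to describe data collection and analysis, and the appendix summarizing study procedures is not shown. This stands in part: exclusivity is inferred from a single trigger with no alternative. But the trigger is a stated rule of data collection. If it is followed as written, no later analysis plan can recover answers that were never collected.

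**The recruitment sentence may mean 30 completers.** It may, with replacement if needed. Replacement would restore the number but not remove the selection. A reader might also infer that the mean is presented as that of all 30 enrolled. The article does not say so.

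**The t tests are not named as the gate.** A reader might infer that these tests alone decide public release. The documents do not support that. The wording is positive usability outcomes and the results of Objective 2. Those results also include focus groups of randomly selected participants, not stated to be limited to completers, and possibly content analysis of saved conversations. Both could reveal failed or abandoned dialogues, although neither enters the tested means.

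**Single-scale rates may overstate the error.** Two scales are tested. If both must pass, which is not stated, the rates are lower, as the table shows. The relative increase remains.

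**Completion may be high and the consequences limited.** Training, a user guide, reminders and compensation on completing each objective all support completion. Objective 3 measures usability and acceptability again every 2 months, negative outcomes return the version for improvement, and chat logs are reviewed weekly. These points limit the harm of a wrong decision but do not correct the Objective 2 means.

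**Rating after a standard exposure is defensible.** It is, and completers would still be rated after 20 conversations under the fix below.

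**Conclusion.** The point holds as a likely upward bias of unknown size. As written, participants who stop before 20 conversations contribute no UMUX-Lite, AES or Technology Acceptance Model scores, and the means set against 68 and 24 are a main quantitative input to the decision on Objective 3.

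The size depends on a completion rate and a score-completion correlation that the article does not give. Under the assumptions shown, losing one participant in ten roughly doubles to more than triples the 5% error of a single test, and losing one in five takes it to 13-36%. The rates for two scales that must both pass are lower but rise in similar proportion. If nearly everyone completes, the effect is small. If stopping is unrelated to usability, there is no bias, only fewer scores. None of the percentages should be read as this study's actual error rate.

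Severity: should-fix, not a fatal flaw. Exclusivity is inferred, the t tests are not the sole gate, and Objective 3 measures the same outcomes again.

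**What to change.** Change the survey rule in the Objective 2 Overview and carry it into each subprotocol:

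- Send the survey to every enrolled participant at the 20th conversation, the end of week 3 or withdrawal, whichever comes first.
- Run the two threshold tests on all who used the chatbot at least once and answered.
- Report the proportion reaching 20 conversations beside the scores, as a usability result in its own right.
- Show completers only as a sensitivity analysis.

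The cost is about one sentence in the master protocol, a time-based trigger in the survey tool and, where a version is already approved, an ethics board amendment. The small downside is that some ratings will come after fewer than 20 conversations, which the sensitivity analysis makes visible. Some early stoppers may still not answer, so the number surveyed and the number answering should both be reported. The change has to be made before Objective 2 data collection.
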